**Figure 1 F1:**
[figure not shown]
Patient selection and recruitment.

### Data collection procedure

3.3

Both hospitals have digital medical records which will be used to collect individual patient data. Furthermore, we will use the variables collected for the cross-sectional study as baseline data. These variables include demographic and clinical characteristics (patient who has the PSA determination as part of opportunistic screening or due to the presence of symptoms suggestive of disease), setting (primary care or clinical service), toxic habits, previous history of cancer, family history, present pharmacological treatment, PSA tests carried out in the last 12 months and PSA value, anthropometric measures and other comorbidities (Table 1).

**Table 1 T1:**
[figure not shown]
Information to be extracted from the medical history.

We will follow both cohorts (positive and negative PSA results) for 2 years by reviewing their medical records (every 3 months for patients with a positive PSA result and annually for patients with a negative result). The following variables will be recorded: diagnostic interventions (digital rectal exam, biopsy, PSA determination, imaging tests), clinical interventions (medical consultations) and therapeutic interventions (radiotherapy, surgery, chemotherapy, hormonal treatment) during follow-up, collecting for each intervention the date and result obtained; and cancer diagnosis (date and cancer type).

### Outcomes

3.4

The study outcomes associated with specific objective 1 are:

1.The effect size of the associations between clinical and analytical factors and false positive result in the determination of serum PSA levels (defined as positive result: if the total PSA value is >10 μg/L or a total PSA between 4 and 10 μg/L if the value of the free PSA/total PSA fraction is <25% in at least in 2 determinations and the result of digital rectal examination(s) and/or subsequent biopsy or biopsies are negative, according to the latest recommendations of the European Association of Urology^[20]^).2.The effect size of the associations between clinical and analytical factors and false negative result in the determination of serum PSA levels (defined as false negative result: if the PSA value is negative, and the patient is diagnosed with PCa in the subsequent follow-up, 2 years, according to the latest recommendations of the European Association of Urology^[20]^).

While for specific objective 2 the study outcomes are as follows:

1.Frequency of patients with appropriate diagnostic interventions performed in those with a positive serum PSA value according to “EAU - ESTRO - ESUR - SIOG Guidelines on Prostate Cancer”.^[32]^ Which is defined as strategies that satisfies or not satisfies EAU recommendations with regard to the following issues (Recommendations for clinical diagnosis of prostate cancer and Recommendations for repeat-biopsy imaging)2.Frequency of prostate cancer patients with an appropriate therapeutic interventions according to “EAU - ESTRO - ESUR - SIOG Guidelines on Prostate Cancer”.^[32]^ Which is defined according to the EAU recommendations with regard to the number and type of therapeutic interventions carried out after prostate cancer diagnosis. The following information will be considered: surgical treatments, radiotherapeutic treatments, active therapeutic options outside surgery and radiotherapy.

Two researchers will independently analyze diagnostic, and therapeutic interventions performed after a positive PSA value the follow-up deadline, and their adaptation to the latest available recommendations.^[32]^ Each patient will be classified as “Appropriate according to guideline”, “more intensive than guideline” or “less intensive than guideline”.

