### Statistical analysis

3.5

The analysis will be performed using the Stata IC 15 program.

-Specific objective 1. We will calculate the proportion of false positive and false negative results for the diagnosis of PCa and the associated variables. In the case of false positive tests, we will also describe the time from a positive PSA result until PCa is ruled out using mean, standard deviation or median and interquartile ranges for the total population and relevant subgroups. In order to analyze clinical and analytical factors associated with the presence of false positive and false negative results in PSA determinations, we will calculate prevalence ratios and their 95% confidence interval with log-binomial regression.-Specific objective 2. We will assess the probability of having a diagnostic, surgical or therapeutic intervention according to variables using risk ratios with their 95% confidence intervals. If necessary, we will adjust for potential confounders using log-binomial regression. We will also evaluate the agreement between the interventions performed and the available guidelines.^[20]^ We will evaluate the inter-observer agreement in the determination of appropriateness using the Kappa index.

Steps will be taken to prevent missing data (e.g., we will periodically review medical records and access data from different sources such as records of primary, specialized and hospital care), but some level is unavoidable and we will incorporate methods analyzing missing data or data from uncertain sources when necessary.^[33,34]^

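### The false-positive definition accepts a negative rectal examination on its own and does not require the man to stay free of a prostate cancer diagnosis over the 2-year follow-up, unlike the false-negative definition

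*Protocol article*

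**What the plan says.** All references are to the protocol article.

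- **Section 3.4, false positive.** A man with a positive PSA is a false positive when "the result of digital rectal examination(s) and/or subsequent biopsy or biopsies are negative". The sentence carries a guideline qualifier, "according to the latest recommendations of the European Association of Urology", whose content is not reproduced. It states no time window.
- **Section 3.4, false negative.** The result is a false negative "if the PSA value is negative, and the patient is diagnosed with PCa in the subsequent follow-up, 2 years". The same guideline qualifier follows.
- **Section 3.3, text after Table 1.** "We will follow both cohorts (positive and negative PSA results) for 2 years by reviewing their medical records", every 3 months for PSA-positive men and annually for PSA-negative men. The date and result of each rectal examination and biopsy are recorded, as are the date and type of any cancer diagnosis.
- **Section 3.5.** "We will calculate the proportion of false positive and false negative results for the diagnosis of PCa", with prevalence ratios from log-binomial regression for the associated factors. For false positives the plan will also "describe the time from a positive PSA result until PCa is ruled out".

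**The concern.** The two halves of specific objective 1 are reported as errors for the same target condition but are judged by different standards. A false negative is established by cancer diagnosis over a fixed period. A false positive is established by whichever of two tests happened to be done, and one of them, the rectal examination, can be normal in a man with cancer. A man with a normal examination in month 2 and a cancer diagnosis in month 18 satisfies the wording, although his diagnosis sits in the study's own data.

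Three outputs rest on this definition:

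- **The false-positive proportion** can include men with cancer. PSA-positive men with neither test belong to no category, so its denominator is also unsettled.
- **The time to rule-out** can end on an examination date or a biopsy date, which are not comparable events.
- **The prevalence ratios** can be affected if work-up differs between men. The Introduction says comorbidity and the Charlson index bear on the decision to request a biopsy. A factor linked to less biopsy could then appear to be linked to false positives.

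**Working it through.** **The wording, side by side**

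| Element | False positive | False negative |
|---|---|---|
| Reference standard | Rectal examination and/or biopsy negative | Prostate cancer diagnosis |
| Period in the definition | None | 2 years |
| Uses the recorded cancer diagnosis | No | Yes |
| Men with no work-up | No class | Not a false negative unless diagnosed |

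The *or* in *and/or* makes a negative examination sufficient. The guideline qualifier is attached to both definitions, yet for false negatives the 2-year criterion is still written out. The qualifier therefore cannot be assumed to supply a biopsy requirement or a diagnosis-free period for false positives.

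**Size (illustration only)**

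The plan gives no false-positive figure to reproduce.

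Inputs from section 3.2.2: sensitivity 21%, specificity 91%, prevalence 5%, 865 evaluable PSA-positive men, precision 2% (read as 2 percentage points).

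Assumed, not in the document:

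- share of men classed on rectal examination alone, *d*: 25%, 50% or 100%;
- share of cancers the examination misses, *m*: 30%, 50% or 70%;
- every man without cancer is classed as a false positive.

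1. PPV = 0.21 × 0.05 / (0.21 × 0.05 + 0.09 × 0.95) = 0.0105 / 0.0960 = 10.9%.
2. Cancers among the positives = 865 × 0.1094 = 94.6. Men without cancer = 770.4, or 89.1%.
3. Men with cancer counted as false positives = 94.6 × *d* × *m*.
4. Resulting proportion = (770.4 + 94.6 × *d* × *m*) / 865.

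| *d* | *m* = 30% | *m* = 50% | *m* = 70% |
|---|---|---|---|
| 25% | 7.1 men, 89.9% | 11.8 men, 90.4% | 16.6 men, 91.0% |
| 50% | 14.2 men, 90.7% | 23.7 men, 91.8% | 33.1 men, 92.9% |
| 100% | 28.4 men, 92.3% | 47.3 men, 94.5% | 66.2 men, 96.7% |

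A shift of 2 points is 0.02 × 865 = 17.3 men. It is passed when *d* × *m* exceeds 17.3 / 94.6 = 18%, which happens in five of the nine cells.

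The group against which false positives are contrasted is only about 95 men. The share of it moved to the wrong side is *d* × *m*, from 0.25 × 0.30 = 7.5% to 1.00 × 0.70 = 70%.

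**Sensitivity to the cancer share.** The 21% and 91% refer to a PSA of 4 μg/L. The study's positivity rule also uses the free/total fraction and at least two determinations, so the cancer share may differ. With an assumed share of 25% (216 cancers, 75.0% without cancer), the same grid gives about 16 to 151 men and a proportion of 76.9% to 92.5%.

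**The case against.** The strongest reply is that the definition should be read in context. Section 3.5 speaks of prostate cancer being ruled out, all positives are followed for 2 years with quarterly record review, and the plural examinations and biopsies suggest whatever work-up occurred over that time. On this view *and/or* merely describes routine practice.

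Part of this stands. A reader might infer that a man whose biopsy shows cancer counts as a false positive because his rectal examination was normal. The text does not exclude this, but it is a strained reading: such a man has not had cancer ruled out. A reader might also infer that the study has no time horizon. It has one; it is simply not carried into this definition.

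Context does not cure the rest. A man classed on a normal examination without biopsy fits the definition on its plain meaning, and nothing says that a later diagnosis reverses his class. Men with no work-up remain unclassified on any reading.

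It is also fair to object that the size is not established. With *d* at 25%, even a 70% miss rate gives 16.6 men, or 1.9 points, which is inside the planned precision. Finally, a 2-year diagnosis rule does not remove dependence on work-up: a man who is never investigated is unlikely to be diagnosed and would be classed as a false positive. That is correct and limits what the fix can claim.

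**Conclusion.** The point holds as a fault in a stated outcome definition. It accepts a negative rectal examination alone, ignores cancer diagnoses that the study will record, and leaves uninvestigated positives without a class. That men with cancer can be counted as false positives follows from the wording; how many cannot be known from the document.

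On the planning inputs and the assumed ranges, it is about 7 to 66 of 865 men, taking the proportion from 89.1% to between 89.9% and 96.7%. The upper end supposes that every man is classed on the examination alone and that 70% of cancers are missed, so it is a ceiling. A reader might conclude that the error is sure to exceed the 2-point precision; the grid does not support that. Nor does the document allow the bias in the prevalence ratios to be calculated: its direction and size depend on how work-up varies with each factor.

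**What to change.** Reword the false-positive outcome in section 3.4 and carry it into section 3.5:

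1. Define a false positive as a positive PSA with no prostate cancer diagnosis in the 2-year follow-up. Date the positive result from the determination that completes the positivity criterion, since that criterion can need at least two determinations.
2. State that any prostate cancer diagnosis in that period excludes false-positive status.
3. Split false positives into biopsy-negative and not biopsied (rectal examination or imaging only, or no work-up). The time to rule-out is then best shown within these groups.
4. Repeat the false-positive proportion and the prevalence ratios in biopsied men as a sensitivity analysis.

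The split and the biopsied-only analysis are needed parts of the change. The 2-year rule alone removes diagnosed cancers but leaves undiagnosed ones among the false positives.

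**Cost.** Outcome and analysis wording only; section 3.3 already lists the dates and results required. The downside is that unbiopsied men are classed on their records, so partial verification remains and should be reported as a limitation. The biopsied-only analysis is smaller and covers a selected group.

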#### Sample size and recruitment procedure

3.2.2

According to a review by the American Cancer Society,^[31]^ a value of PSA of 4 μg/L had an estimated sensitivity of 21% to detect any type of prostate cancer and a specificity of 91%. We estimate a prevalence of PCa in this population not lower than 5% (given that we include asymptomatic and symptomatic patients), with a 95% margin of error and 2% precision, we will need to include 457 patients with a negative PSA result and 865 PSA-positive patients. Taking into account a 20% possible loss during follow-up, we will increase to 572 patients with a negative PSA result (286 per center) and 1081 patients with a positive PSA result (541 per center) who will be selected consecutively from among those included in the previous cross-sectional study (NCT03968692) until we reach the proposed sample size. We will use the initial randomized list (which included determinations during the first 4 months of 2018) to select patients who meet both negative and positive PSA criteria and if it is necessary, we will continue to review analyses until the sample size is achieved. (Fig. 1)

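### The PSA-negative cohort is sized for a proportion, but its outcome is a set of association ratios resting on about 20 to 29 cancers that count only if routine care finds them

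*Protocol article*

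**What the plan says.** Protocol article, section 3.4 (Outcomes) sets as an outcome "The effect size of the associations between clinical and analytical factors and false negative result in the determination of serum PSA levels". The event is a negative PSA where "the patient is diagnosed with PCa in the subsequent follow-up, 2 years". For objective 1, section 3.5 (Statistical analysis) plans the proportion of false negatives and then states that "we will calculate prevalence ratios and their 95% confidence interval with log-binomial regression".

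Section 3.2.2 (Sample size) uses an "estimated sensitivity of 21% to detect any type of prostate cancer" and a specificity of 91%. It adds "We estimate a prevalence of PCa in this population not lower than 5" per cent. The target is set "with a 95% margin of error and 2% precision", and the result is that "we will need to include 457 patients with a negative PSA result and 865 PSA-positive patients". After a 20% allowance for loss, the negative cohort becomes 572. No effect size or power is given for an association.

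Section 3.3 (Data collection) plans follow-up by record review, annually for PSA-negative men. It records examinations, biopsies, PSA tests and imaging with dates and results. No study biopsy or other uniform reference test is planned for PSA-negative men. The limitations in section 4 (Discussion) cover record quality, missing health-status tools, loss to follow-up and the inability to assess overdiagnosis.

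**The concern.** There are two problems, and they compound each other.

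The first is size. A cohort large enough to place one proportion within 2 points need not be large enough to estimate ratios between subgroups. What governs a ratio is the number of events, and with a rare event that number is small. Ratios from so few events are imprecise, and those that reach significance will tend to be exaggerated.

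The second is what the event measures. A PSA-negative man with cancer becomes a false negative only if someone investigates him within two years; otherwise he is analysed as a true negative. Several recorded characteristics (symptoms, requesting setting, family history, PSA tests in the previous 12 months) plausibly also influence who is re-tested or biopsied. Their ratios then mix the chance that PSA missed a cancer with the chance that the cancer was looked for. A larger cohort would not remove this. Section 4 expects the results to support new recommendations, so it matters which of the two is being estimated.

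**Working it through.** **Inputs** (section 3.2.2): sensitivity 0.21, specificity 0.91, prevalence 0.05 (a floor), 95% confidence, half-width 0.02, loss 20%.

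**1. The plan's own figure.** n = 1.96² × p(1−p) / 0.02². With p = 0.05, n = 456.2, so 457; 457/0.8 = 571.25, so 572. The stated numbers reproduce as a single-proportion precision calculation at 5%.

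**2. Risk of a false negative from the stated accuracy.** 1−NPV = 0.05×0.79 / (0.05×0.79 + 0.95×0.91) = 0.0395/0.904 = 4.37%. Put into the formula in step 1, this would give 402 rather than 457, so the plan in effect used 5%. Both values are carried forward.

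**3. Expected events.**
- 457 × 4.37% = 20.0; 457 × 5% = 22.9.
- 572 (no losses) × 4.37% = 25.0; 572 × 5% = 28.6.
- Assumption: routine care finds half of the 20, giving 10.
- Assumption: prevalence is 10%. Then 1−NPV = 0.079/(0.079 + 0.819) = 8.8%, giving 40 (n = 457) to 50 (n = 572).

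**4. Detectable ratio for one binary factor.** Let f be the share exposed and p the overall risk. Then p0 = p/(1−f+f·RR) and p1 = RR·p0. Power = Φ{[(p1−p0) − 1.96·SE0]/SE1}, where SE0 uses the overall risk and SE1 the separate risks.

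Example with n = 457, p = 0.0437, f = 0.3, RR = 3.5: p0 = 0.0250, p1 = 0.0874, SE0 = 0.0209, SE1 = 0.0256. Power = Φ{(0.0624 − 0.0409)/0.0256} = Φ(0.84) = 80%.

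| n | risk | events | ratio at 80% power, f = 20% / 30% / 50% |
|---|---|---|---|
| 457 | 4.37% | 20 | 3.6 / 3.5 / 4.15 |
| 572 | 5% | 29 | 2.9 / 2.8 / 3.1 |
| 457 | half detected (assumption) | 10 | 6.2 / 6.7 / 14.9 |
| 457 | 8.8% (assumption) | 40 | 2.5 / 2.35 / 2.45 |
| 572 | 8.8% (assumption) | 50 | 2.3 / 2.15 / 2.2 |

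For a true ratio of 2 with 457 men and 20 events, power is 33 to 38%.

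**5. Expected interval.** Same setting, ratio 2, f = 0.3: 9.2 exposed and 10.8 unexposed events are expected among 137.1 and 319.9 men. SE(log RR) = √(1/9.2 − 1/137.1 + 1/10.8 − 1/319.9) = 0.437. The 95% interval is 2 × exp(±1.96 × 0.437) = 0.85 to 4.7. At f = 20% or 50% it runs from about 0.8 to 4.9 or 5.0.

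**6. A joint model, if one is fitted.** The Introduction and section 3.3 together name about 14 candidate characteristics. Taking 12 as an illustration, 20/12 = 1.7 and 28.6/12 = 2.4 events per factor; 40 to 50 events give 3.4 to 4.2. In a simulation of 300 datasets with 12 factors of no true effect and 457 men at 4.37%, about 35% of log-binomial fits failed or showed separation. Among the fits that held, about 20% of the null ratios for the binary factors fell outside 0.5 to 2. With 572 men, about 19% of fits failed.

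**7. Verification.** If a share d of cancers is detected in each group, the observed ratio equals the true ratio × d1/d0. As an illustration with assumed shares, suppose two groups have the same true risk of 4.37% but 60% of cancers are found in one and 30% in the other. The observed risks are 2.6% and 1.3%, a ratio of 2.0 produced by work-up alone. The documents give no detection or biopsy rates, so the actual size is unknown.

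**The case against.** The strongest reply is that the study is an estimation study. It plans confidence intervals, states no hypothesis test, and is adequately sized for the proportion it names. Section 3.4 also says openly what is counted, and section 3.3 already collects the work-up data. All of this stands. It does not answer the point that the named outcome is an effect size, for which the expected interval runs from about 0.8 to 5 when the true ratio is 2.

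It is also fair that 5% is a floor and events could be more numerous. The 10% case therefore belongs in the range, and it brings the detectable ratio down to about 2.2 to 2.5. Incomplete detection pushes the other way.

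A reader might infer more than the documents support:
- *That a dozen factors will enter one model.* No covariate list or joint model is stated for objective 1, Table 1 is not shown, and single-factor ratios fit the text equally well. Step 6 is conditional.
- *That the men are largely unbiopsied, or that the ratios reflect work-up as much as missed cancer.* No biopsy rate is given and neither share can be quantified. Only the mechanism follows from the definition.
- *That the investigators claim causes.* They write of associations throughout.
- *That missing modelling detail is itself a fault.* Covariate limits and sparse-data methods may sit in an analysis plan not shown. The cohort size and event definition, however, are fixed here.

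**Conclusion.** The point holds in limited form. The PSA-negative cohort is sized for a proportion, while the outcome is association ratios. On the plan's own inputs there will be about 20 to 29 events, with a range of about 10 to 50 under the two stated assumptions. With 457 men and 20 events, only single-factor ratios of about 3.5 to 4.2 are detectable with 80% power; in the most favourable planning case (29 events, no losses) the figure is about 2.8 to 3.1. These figures assume a binary factor with 20 to 50% exposed and a two-sided 5% level.

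Separately, because the event depends on diagnosis in routine care, the proportion is a lower bound for false negatives, and the ratios can reflect differential work-up. The size of that bias cannot be derived from the documents, but the stated limitations omit it. The descriptive proportion remains worth reporting. What should change is its label and the weight placed on the ratios.

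**What to change.** - Describe the outcome as prostate cancer diagnosed within two years of a negative PSA, and its proportion as a lower bound for false negatives. Add incomplete and possibly differential verification to the limitations.
- Report re-testing, imaging and biopsy during follow-up by each candidate factor, using data already collected under section 3.3, and interpret the ratios alongside that table.
- Label the false-negative associations exploratory. Use a method suited to sparse events (penalised regression or exact intervals, for example), with few pre-named covariates in any adjusted model.
- State the detectable ratio or the expected interval width, with the event range behind it.
- Include symptomatic versus opportunistic testing as a factor or descriptive breakdown. Do not model the two groups separately, since an even split of about 20 events leaves about 10 in each.

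No extra patients or tests are needed. The cost is revised wording, one further table, slightly more analysis and a more modest claim.

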### Specific objectives

2.2

1.To analyze the clinical and analytical factors associated with the presence of false positive and false negative results in PSA determinations in patients undergoing opportunistic screening or with symptoms suggestive of disease.2.To evaluate the patient's clinical outcome, and any diagnostic and/or clinical and/or therapeutic interventions over a 2-year period after PSA testing. Furthermore, we will study whether this management is appropriate to the recommendations of the European Association of Urology.

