#### Eligibility criteria

3.2.1

Participants will be a random sample of men from the Health Departments 17 and 19, in the Valencian Community (these include 20 primary health centers and 2 hospitals: General University Hospital of Sant Joan d’Alacant and General University Hospital of Alicante, respectively). These are referral hospitals for all individuals living in their catchment areas and belong to the National Health Care System (the majority of the population in Spain uses the National Health System (NHS) as the main medical service (the publicly funded insurance scheme covers 98.5% of the Spanish population). We will include men over 18 with a PSA determination requested in a routine health examination from January to April 2018. Patients who do not belong to the NHS or have been previously diagnosed with PCa or who are being followed for previous high PSA values will be excluded.

We will select a cohort of patients with positive PSA results (defined as total PSA value is >10 μg/L or a total PSA between 4 and 10 μg/L if the value of the free PSA/total PSA fraction is <25% in at least in two determinations) and a cohort of patients with negative results (defined as total PSA value is < 4 μg/L or a total PSA between 4 and 10 μg/L if the value of the free PSA/total PSA fraction is >25%) among subject included in a previous cross-sectional study (NCT03968692) that we are carrying out (registered in ClinicalTrials.gov (NCT03968692)). This cross-sectional study aims to describe the PSA determinations that are performed in clinical practice and their appropriateness according to the available recommendations, considering sociodemographic and clinical characteristics of the patients.

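### Appropriateness of care is not tied to the guideline edition in force when care was given, and the therapeutic outcome sets no minimum record after diagnosis, so some men can be misclassified

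*Protocol article*

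**What the plan says.** Both outcomes of specific objective 2 (Protocol article, section 3.4) are frequencies of care that meets the European Association of Urology (EAU) guidance: diagnostic care in men with a positive PSA, and treatment in men with prostate cancer. Both cite reference 32. Two researchers are to assess "diagnostic, and therapeutic interventions performed after a positive PSA value the follow-up deadline" and "their adaptation to the latest available recommendations", again with reference 32. Each patient goes into one of three classes: appropriate, more intensive than the guideline, or less intensive.

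The therapeutic outcome rests on the "number and type of therapeutic interventions carried out after prostate cancer diagnosis". The observation period is counted from the test: section 2.2 speaks of "therapeutic interventions over a 2-year period after PSA testing", and section 3.3 says "We will follow both cohorts (positive and negative PSA results) for 2 years by reviewing their medical records". Eligibility (section 3.2.1) requires a "PSA determination requested in a routine health examination from January to April 2018", and section 3.2.2 allows review of further tests if the sample size is not reached.

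Section 3.5 adds: "We will also evaluate the agreement between the interventions performed and the available guidelines", this time citing reference 20. Section 3.3 also states that the date of every intervention and of any cancer diagnosis will be recorded.

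**The concern.** There are two separate weaknesses in how the outcome is fixed.

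The first is the yardstick. A clinician can follow only the edition that exists when the decision is made. If the standard is whichever edition is newest when the researchers classify, earlier care may be scored against text that was not yet issued. If the standard is the single document cited as reference 32, one edition is still applied to more than two years of care. Citing a different reference for the agreement analysis leaves the reader unsure which document is the standard.

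The second is observation time. Treatment is counted from diagnosis, but the clock stops 2 years after the PSA test. A man diagnosed in month 22 has 2 months in which treatment can appear in his record. He must still be placed in one of three classes, none of which means that it is too early to say. If unfinished treatment is scored as it stands, the error runs towards the less-intensive class.

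What is at stake is the frequency of appropriate care, which is the result of specific objective 2.

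**Working it through.** No figure in the article depends on this point, so there is none to reproduce. The checks are calendar arithmetic, a comparison of the sections, and an illustration of how many men could have a short record.

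**Calendar.** Index tests run January to April 2018 (section 3.2.1). Adding 24 months, follow-up ends January to April 2020. The judged care therefore spans up to 4 + 24 = 28 months, or more if recruitment is extended under section 3.2.2.

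**Yardstick, section by section.**
- Section 3.4, objective 2 outcomes and researcher assessment: reference 32, described as the latest available.
- Section 3.4, definitions of false positive and false negative: reference 20, also described as the latest EAU recommendations.
- Section 3.5, agreement of interventions with guidelines: reference 20.

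Two references are each used as the current EAU standard, and the appropriateness outcome and its analysis cite different ones. No sentence links an edition to the date of an intervention.

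**Expected PSA-positive cancers.** Inputs from section 3.2.2: sensitivity 0.21, specificity 0.91, prevalence 0.05, 865 positive men after loss and 1081 before loss (865 / 0.8 = 1081.25).
- Positive predictive value = (0.21 × 0.05) / (0.21 × 0.05 + 0.09 × 0.95) = 0.0105 / 0.0960 = 0.1094.
- 865 × 0.1094 = 94.6, and 1081 × 0.1094 = 118.2, so about 95 to 118 cancers.

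This applies the quoted accuracy of a cut-off of 4 μg/L to the study's own, more complex definition of a positive result, so it is an order of magnitude.

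**Share diagnosed in the last w months of the 24.** The documents give no distribution of time to diagnosis, so this is assumed. For uniform timing the share is w / 24. For exponential timing with mean m it is [F(24) − F(24 − w)] / F(24), with F(t) = 1 − exp(−t/m).

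| Assumed timing | Under 3 months of record | Under 6 months of record | Men under 6 months (of 95 to 118) |
|---|---|---|---|
| Exponential, mean 3 months | 0.06% | 0.2% | about 0 |
| Exponential, mean 6 months | 1.2% | 3.2% | 3 to 4 |
| Exponential, mean 12 months | 4.4% | 10.2% | 10 to 12 |
| Uniform over 24 months | 12.5% | 25% | 24 to 30 |

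**Worst-case effect on the reported frequency.** Suppose a true proportion p is appropriate, and every such man with a short record (share f) is scored as less intensive. The reported frequency is then p(1 − f). With an assumed p = 0.80, it is 0.80 × 0.998 = 0.798 at f = 0.2%, 0.80 × 0.90 = 0.72 at f = 10%, and 0.80 × 0.75 = 0.60 at f = 25%. These are outer limits, because researchers need not score every short record that way.

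**The case against.** The strongest reply has five parts.

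1. The phrase about the latest recommendations carries a citation to one named document, so a fixed edition is at least as natural a reading as a moving one. This stands: a reader might infer a floating standard, but the text does not settle it. The concern survives either way, because a fixed edition is not tied to the date of care either.

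2. A reader might infer that care will be misclassified. The documents do not support that. It would need relevant recommendations to have changed, which they do not show, and researchers to score pending treatment as too little, which they do not say. Dates are recorded, so a recent diagnosis is visible. The Introduction also recognises active surveillance, so little early treatment need not count as under-treatment. This stands: misclassification is possible, not demonstrated.

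3. A reader might infer that truncation falls hardest on false negatives and so creates a spurious link between PSA result and under-treatment. The assessment sentence covers care after a positive PSA, and section 3.5 states no comparison of appropriateness by PSA result. Only the wider wording of the therapeutic outcome, men with prostate cancer, leaves the question open. The inference is not supported.

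4. A reader might extend truncation to both outcomes. Diagnostic care is counted from the positive PSA, and planned follow-up from the test is 2 years for everyone, so the mechanism applies to the therapeutic outcome alone.

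5. A condensed article may leave edition matching and late diagnoses to the full protocol, the sentence with the deadline lacks a word and may only bound which interventions count, and the reference list is not shown, so whether references 20 and 32 differ in content cannot be checked. This limits the force of the point. But the article does state the standard and the observation period, and it cites the standard inconsistently.

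**Conclusion.** The point holds in a limited form. The standard for appropriateness is not tied to the date of care over a span of up to 28 months, and sections 3.4 and 3.5 cite different references for it. The size of this effect cannot be given, because it depends on changes between editions that the documents do not describe.

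For the therapeutic outcome, unequal time after diagnosis can push late-diagnosed cancers towards the less-intensive class. Its size ranges from negligible to material, depending on the assumed timing in the table. The uniform case, at the top of the range, is probably pessimistic for men whose positive test itself prompts work-up. The case count rests on the plan's own accuracy and prevalence inputs, and 6 months is only an illustrative threshold.

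The change is worth making because it is cheap and removes an avoidable source of error from a main result of specific objective 2. No sample size figure is affected.

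**What to change.** - In section 3.4, state that each intervention is judged against the EAU edition in force on its recorded date. A comparison with one later edition can be reported as a secondary view.
- Cite the same guideline for appropriateness in sections 3.4 and 3.5.
- Repair the sentence on the follow-up deadline, and say whether cancers found in PSA-negative men are classified.
- Classify therapeutic appropriateness only in men with a common minimum record after diagnosis, with the length set by the investigators before classification starts. Report the others, with their number, as not yet assessable.

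The cost is mainly wording, since intervention and diagnosis dates are already collected. The researchers need dated guideline editions. Somewhat fewer cancers are classified: with a 6-month minimum, the number left out would be the last column of the table. The therapeutic result then describes men diagnosed early enough to be observed, and should be labelled so.
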